### Statistical analysis

The statistical analysis will be undertaken in accordance with the intention-to-treat (ITT) principle. The ITT analysis will include all participants, including those who do not fully adhere to the protocol and those with missing outcome data. A per-protocol analysis will also be performed where appropriate. Demographic and clinical characteristics as well as baseline data will be presented to assess the baseline comparability of the two groups. Differences from baseline to each time point will be calculated for all primary and secondary outcomes. Descriptive statistics will be presented for each group as mean change, standard deviations and confidence intervals (CI) for continuous variables, and frequencies and percentages for categorical variables. A longitudinal repeated measures design will be used to assess changes from baseline, and to make between group comparisons for the continuous outcome measures. Between group comparisons will be made immediately post treatment (1 week residential group; 6 weeks outpatient group) and at 12 weeks.

The effect of the interventions over time will be compared using linear and mixed models. These models are chosen as they appropriately adjust for correlation that occurs from collecting multiple observations per participant [37]. At the 1,6 and 12 week time points, continuous variables will be analysed using a mixed model repeated-measure analysis of variance (ANOVA) model (with treatment as the between group factor and time as the repeated factor). The non-parametric equivalent or data transformation will be used if non-normal distributions apply. Where significant differences occur, post-hoc comparisons will be conducted using Tukey’s multiple comparison procedure. Differences in nominal/ordinal data will be analysed using the *χ*
^2^ test. A significance level of 0.05 will be set for any inferential statistics conducted. The inclusion of the post treatment (T2) measure may help reveal if any differences occur as a consequence of the different interventions (as T2 reflects the immediate post-treatment scores for each group). However, this is based on the assumption that any changes in outcome from T1 and T2 (over 1 and 6-weeks) are linear, and also between T2 and T3. We recognise if the trend is non-linear then we will have insufficient data points to model the outcome over time in a way that will enable us to compare the trajectory of patient outcomes using the 3 time points. If interim analysis reveals this to be the case, we will remove T2 measures from the final analysis.

Secondary analysis will be undertaken to assess the predictors of outcome at the primary endpoint (12 weeks post treatment commencement) in both groups, using multiple regression analysis. Predictor variables including age, gender, baseline pain, physical function, duration of symptoms, mood/anxiety, self-efficacy, co-morbidities and exercise adherence will be measured. Analyses will be performed separately for MDT and IP group treatments. Response variables will be change in HAGOS function in daily living score pre and post intervention (MCID > 5.2 points) and numeric pain rating on the VAS. All predictors will be checked for collinearity. Univariate logistic regression will be performed on all potential predictors and those associated with the outcomes will be entered into the multivariate logistic regression model. Variables with the lowest predictive value will be removed from the model if *p* > 0.05. Odds ratios and 95 % CI’s will be calculated for all final predictors.

No statistical adjustment will be made for multiple testing. All tests will be two-sided and carried out at the 5 % level of significance. Changes to the study design or analysis plan will be documented with full justification. A statistician will oversee the blinded analyses of the data. The statistical analysis procedure will be discussed, reviewed and co-worked with statisticians at the Department for Health University of Bath, and School of Clinical Sciences at Bristol University.

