### Design

The study is a superiority parallel-group, randomised controlled trial (RCT) of a 7-day residential, multidisciplinary intervention (MTD programme), and individualised physiotherapy outpatient care (IP programme) with 3-month follow-up. Measurements will be taken at baseline, post-treatment (7-day MDT; 6-weeks IP) and 12-weeks. We considered including a sham control treatment group but felt in a well-motivated young military cohort this could have a negative impact on recruitment. Trial participants, assessors and clinical/research staff will be un-blinded to treatment allocation. The protocol will conform to the CONSORT (Consolidation of Standards of Reporting Trials) guidelines for non-pharmacological interventions [25], and principles of the Declaration of Helsinki [26].

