### Randomisation and treatment allocation concealment

A block randomisation method will be used to randomise subjects into groups that result in equal sample sizes. This method will ensure a balance in sample size across both groups over time. Blocks are small and balanced with pre-determined group assignments, which keeps the numbers of subjects in each group similar at all times, whilst ensuring there is a 50:50 likelihood of participants being allocated to either group. Due to the possible influence of gender on the efficacy of strengthening exercise [32, 33], the study will only recruit male participants. After patient eligibility has been confirmed and informed consent obtained, a sealed envelope will be opened to reveal group allocation by an independent administrator not involved in the recruitment, treatment or assessment of study outcomes. A plain language statement will inform participants that they have an equal chance of receiving the residential MDT or individualised outpatient intervention. Group allocation will be documented and communicated to the supervising therapists by the independent administrator. Prior to the study, all treating staff will have received a briefing on the study protocol, the ethical, clinical and scientific basis of the study, the randomisation process and specific intervention for each treatment group, in line with the study protocol. It is not possible, relevant or necessary to blind participants to treatment allocation in this study. The clinical staff supervising both groups will be, by necessity, unblinded. Day and Altman [34] suggest blinding assessment by using non-involved assessors to record outcome scores. This is not possible in our study as independent assessors with specific knowledge of quantification of clinical outcomes are not available due to specialist staff man-power limitations. To minimise the potential influence of outcome assessors, instructions are standardised to ensure consistency in measurement. A medical statistician assisting with statistical analysis will be blind to group allocation until completion of the analysis.

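### The planned post-treatment comparison sets week 1 in the residential arm against week 6 in the outpatient arm, and the interim linearity rule for keeping or dropping that visit does not remove the confounding

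*Protocol article*

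**What the plan says.** The Design section sets three visits per participant: "Measurements will be taken at baseline, post-treatment (7-day MDT; 6-weeks IP) and 12-weeks". The second visit, T2, is therefore tied to the end of each programme and not to a common week.

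The Statistical analysis section uses T2 in four ways:

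- As a test between arms: "Between group comparisons will be made immediately post treatment (1 week residential group; 6 weeks outpatient group) and at 12 weeks".
- In the repeated-measures model, which crosses arm with time: "At the 1,6 and 12 week time points, continuous variables will be analysed using a mixed model repeated-measure analysis of variance (ANOVA) model".
- For attribution: "The inclusion of the post treatment (T2) measure may help reveal if any differences occur as a consequence of the different interventions".
- Subject to a condition and a rule. The attribution is said to assume that "any changes in outcome from T1 and T2 (over 1 and 6-weeks) are linear, and also between T2 and T3". The authors accept that "if the trend is non-linear then we will have insufficient data points to model the outcome over time", and add: "If interim analysis reveals this to be the case, we will remove T2 measures from the final analysis".

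The same section applies no multiplicity adjustment and sends significant results on to Tukey comparisons. The primary time point is 12 weeks in both arms (Study aims and hypothesis; Table 4; Sample size).

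**The concern.** A between-group difference at T2 can arise because the programmes differ in effect, or because one arm has had five more weeks since baseline. The schedule gives every member of an arm the same T2 week, so no model fitted to these data can separate the two. If both programmes produced the same improvement at every week, the T2 test would still tend to show the residential arm behind, and the article's own wording would lead a reader to attribute that to the intervention. Conversely, a real early advantage of the residential programme could be hidden.

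The article discloses an assumption about linearity, but not the unequal timing as a source of bias. Its remedy is therefore aimed at the wrong problem, and it makes the content of the final model depend on a look at the data.

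**Working it through.** **Inputs from the protocol.** T2 is week 1 (residential) or week 6 (outpatient), and final follow-up is week 12 (Design). SD 11, 43 per group after dropout and two-sided 5% come from Sample size. Whether 43 follows from the stated effect and SD is a separate question; here it is only the planned evaluable number.

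**Assumptions not in the protocol.** A 12-week gain G common to both arms, a baseline-to-T2 correlation r of 0.5 to 0.7, and SD 11 holding at T2. The plan gives no figure of its own for the T2 contrast, so there is none to reproduce.

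**1. Can the stated linearity condition be checked?** The condition is linear change within T1–T2 and within T2–T3. A line with a bend at T2 has three parameters (intercept and two slopes). Each arm has three visit means, at weeks 0, 1, 12 or 0, 6, 12. Residual degrees of freedom: 3 − 3 = 0 per arm. Any three means fit perfectly, so no data could contradict the condition as worded. A single straight line through all three visits has two parameters and leaves 3 − 2 = 1 degree of freedom per arm. That stricter condition can be tested.

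**2. Would passing a linearity check protect the T2 contrast?** Let both arms follow the same straight line, G·t/12 at week t. Treatment difference at equal time is zero. Expected T2 difference = G·6/12 − G·1/12 = 5G/12, against the residential arm.

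- G = 5.2: 5 × 5.2/12 = 2.2 points
- G = 10: 5 × 10/12 = 4.2 points

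Linearity holds exactly here, so the rule keeps T2 and the bias stays.

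**3. How often would the test reject?** SD of change = 11·√(2(1 − r)): 11.0 for r = 0.5 and 8.5 for r = 0.7. Standard error of the difference = SD of change × √(2/43): 2.37 and 1.84. Noncentrality = (5G/12)/SE, on a t distribution with 84 degrees of freedom.

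| G | Difference | r = 0.5 | r = 0.6 | r = 0.7 |
|---|---|---|---|---|
| 5.2 | 2.2 | 15% | 17% | 21% |
| 10 | 4.2 | 41% | 49% | 61% |

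The nominal rate is 5%. If SD 11 is itself the SD of change, the r = 0.5 column applies.

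**4. Does this need a straight line?** No. With a common curve 10·(1 − e^(−t/τ)), the T2 difference is 10·(e^(−1/τ) − e^(−6/τ)). This gives 5.6, 5.6 and 4.1 points for τ = 2, 4 and 8 weeks.

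**5. Does it reach the repeated-measures model?** I simulated the three-visit ANOVA with identical linear trajectories, compound symmetry, r = 0.5 and 0.7, and 4,000 runs each. The treatment-by-time interaction rejected 14% and 21% of the time at G = 5.2, and 44% and 64% at G = 10. At G = 0 it rejected about 5%. An omnibus interaction that includes T2 therefore carries the same bias.

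**6. Week 12.** Under the same trajectories the expected difference is G − G = 0. With complete data and a saturated group-by-visit mean model, the estimated 12-week difference is the same with or without T2.

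**The case against.** The strongest reply is that the primary endpoint is change to 12 weeks, measured at the same elapsed time in both arms. That stands. A reader might infer that the main result is biased; the documents do not support this. T2 can affect the 12-week conclusion only through an omnibus test, missing data or covariance constraints.

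Second, programme length is part of what the trial compares, the outpatient arm spends most of those five weeks in treatment, and the Discussion considers natural recovery unlikely. An end-of-programme contrast is then a legitimate pragmatic description. That stands for description, but not for attributing a difference to the interventions as though timing were equal. The gains used above have no source in the protocol, and the bias runs against the hypothesised superior arm, so it does not favour the trial's hypothesis.

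Third, a test, timing and threshold for the interim look may be given in an analysis plan not shown. That is fair, and their absence is not the complaint. The rule would not cure the problem however well it was specified.

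Three further inferences are tempting and go too far:

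- *Three visits cannot test linearity at all.* True only of the segment-wise wording; a single line leaves one degree of freedom per arm.
- *The model has empty week-1 and week-6 cells.* This follows only if those weeks are levels of the time factor. With visits T1, T2 and T3 as levels, no cell is empty.
- *The interim look is unblinded, or T2 dates unblind the statistician.* The article says "A medical statistician assisting with statistical analysis will be blind to group allocation until completion of the analysis". Nothing says that the look uses unmasked arms or that the statistician receives visit dates.

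**Conclusion.** The point holds for the T2 between-group comparison, for any group-by-time test that includes T2, and for the keep-or-drop rule. Arm is fully confounded with five weeks of elapsed time at T2. That conclusion rests on the visit schedule alone and needs no assumption. Its size does: with SD 11, 43 per arm, a common linear 12-week gain of 5.2 to 10 points and a correlation of 0.5 to 0.7, two equally effective programmes would differ by 2.2 to 4.2 points at T2 and be declared different 15% to 61% of the time. These are conditional illustrations and not forecasts.

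The linearity condition cannot be contradicted as worded, and satisfying it would not remove the bias. Deciding on T2 after an interim look is thus a data-dependent model choice that leaves the problem in place. Because the 12-week contrast is sound, this is a should-fix matter and not a threat to the primary result.

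**What to change.** Amend the Statistical analysis section, before outcome data are seen, as follows:

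1. Make week 12 the only between-group comparison, estimated as the group contrast at that visit and not through an omnibus group-by-time test that includes T2.
2. Report T2 as a within-arm, end-of-programme description, with the week of measurement stated for each arm and no between-group p-value. Remove the sentence that attributes T2 differences to the interventions.
3. Delete the interim linearity rule.
4. Decide in advance whether T2 data stay in the mixed model. They may, as an arm-specific occasion. About 15% dropout is expected by week 12, and for participants seen at T2 but not at week 12, T2 is the only post-baseline observation; it can inform the week-12 estimate under missing-at-random. Removing T2 from the model altogether is not required.

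The cost is the loss of a post-treatment between-group p-value. Visits, measurements and sample size do not change.

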### Sample size

The primary endpoint will be change from baseline to 12-weeks in (a) the HAGOS ‘physical function in daily living’ subscale and (b) VAS numeric pain rating. Sample size calculation is based on clinically relevant changes over the study period (e.g., score changes between baseline and follow-up should be, on average, subjectively perceptible by the participant). The minimum clinically important difference (MCID) in the HAGOS subscale has been suggested to be 4.8–5.2 points [53]. Between participant standard deviations have not been widely reported for the VAS using intra-articular hip pain patients [1, 10]. Therefore, the required sample using a MCID of 5.2 between groups on the HAGOS subscale and a standard deviation of 11 points, with a significance level of 0.05 (2 tailed) and a power of 80 %, is 43 per group. Allowing for an estimated drop out rate of approximately 15 % at the 12-week follow-up, a total of 100 participants will be recruited into the study. Based on current referral rates it is anticipated this sample target will be met from routine referrals to DMRC Headley Court and no additional strategies to promote enrolment are required. The sample size was calculated using G*Power software Version 3.0.10 (Franz Faul, Universitaet Kiel, Germany). There is currently no RCT reporting the effects of a residential MDT intervention versus outpatient individualised treatment approaching this sample size in the available literature.

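### The 12-week baseline-adjusted treatment difference is not named as the primary test; the stated route is an omnibus repeated-measures ANOVA followed by Tukey comparisons

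*Protocol article*

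**What the plan says.** The Sample size section sets the target: "The primary endpoint will be change from baseline to 12-weeks in (a) the HAGOS" daily-living subscale, and (b) VAS pain. Study aims and the Table 4 footnote also put the primary time point at 3 months.

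The Statistical analysis section says that between-group comparisons will be made after treatment and at 12 weeks, and that differences from baseline will be calculated. The model it names for continuous outcomes is a mixed-model repeated-measures ANOVA, "with treatment as the between group factor and time as the repeated factor", at weeks 1, 6 and 12. It continues: "Where significant differences occur, post-hoc comparisons will be conducted using" Tukey's procedure. No baseline covariate is mentioned, and neither the interaction nor the 12-week contrast is named as the primary test.

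The same section later refers to T1, T2 and T3 as the three time points, with T2 the post-treatment measure, and says T2 will be removed if an interim analysis shows non-linear trends. It also states: "No statistical adjustment will be made for multiple testing". On categorical outcomes it says: "Differences in nominal/ordinal data will be analysed using the" χ² test.

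**The concern.** The endpoint is one between-group contrast at one time. The named model yields a treatment main effect, a time effect and a treatment-by-time interaction, and pairwise tests come only after significance. The plan does not say which of these decides the trial.

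T2 makes this matter. It falls at week 1 in the residential arm and week 6 in the outpatient arm. A T2 difference may therefore reflect elapsed time, yet an omnibus interaction that includes T2 responds to it as strongly as to a 12-week difference. Whether T2 stays in is itself decided after an interim look at the data.

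Baseline scores are collected on everyone. Not using them as a covariate gives up precision that costs nothing to obtain.

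**Working it through.** **Inputs.** From Sample size: "using a MCID of 5.2 between groups on the HAGOS subscale and a standard deviation of 11 points", and "with a significance level of 0.05 (2 tailed) and a power of 80 %, is 43 per group". The correlation r between baseline and later scores is not given, so r = 0.3, 0.5 and 0.7 are assumed, equal for all pairs of times. The document does not say whether 11 is the SD of the raw score or of the change; both are shown.

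**1. The plan's own figure.** For a plain two-group comparison, n = 2(1.960 + 0.842)² × 11² / 5.2² = 70.2, so 71 per group (72 by the t distribution), not 43. With 43 per group, SE = 11 × √(2/43) = 2.37 and power is 0.58. A figure close to 43 appears only with a correlation that the document does not state: for example 44 per group for a change score at r = 0.7, or for ANCOVA at r = 0.63, with 11 as the raw SD. That is a separate matter; 43 is used below only as the planned number analysed.

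**2. Which levels does time have?**
- *Weeks 1, 6 and 12, as the model sentence lists.* The residential arm has weeks 1 and 12, the outpatient arm weeks 6 and 12. Four of six cells are filled. An additive model already uses four parameters (intercept, treatment, two for time), so no interaction can be estimated.
- *Baseline, T2 and T3, as the T1–T3 text implies.* All six cells are filled and the interaction has 2 df. This reading is used in step 3.

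**3. Interaction with T2 included (raw SD 11, 43 per group).** With d_t the group difference at time t and d̄ their mean, the noncentrality is λ = (n/2) Σ(d_t − d̄)² / [σ²(1 − r)], on F(2, 168).

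Take a T2-only effect, d = (0, 5.2, 0). Then Σ(d_t − d̄)² = 5.2² × 2/3 = 18.03 and λ = 21.5 × 18.03 / [121(1 − r)].

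| r | λ | Interaction significant | 12-week change or ANCOVA test |
|---|---|---|---|
| 0.3 | 4.58 | 46% | about 5% |
| 0.5 | 6.41 | 61% | about 5% |
| 0.7 | 10.68 | 83% | about 5% |

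Simulation (20,000 trials per setting) agrees. The patterns (0, 0, 5.2) and (0, 5.2, 5.2) give the same sum, 18.03, so the omnibus test cannot tell a 12-week effect from a T2-only effect.

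**4. T2 dropped.** The 2×2 interaction is then exactly the two-group test of change to 12 weeks. SD of change = 11√(2(1 − r)); ANCOVA residual SD = 11√(1 − r²); SE = SD × √(2/43).

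| r | Change SD (SE) | Power | ANCOVA SD (SE) | Power |
|---|---|---|---|---|
| 0.3 | 13.02 (2.81) | 0.45 | 10.49 (2.26) | 0.62 |
| 0.5 | 11.00 (2.37) | 0.58 | 9.53 (2.05) | 0.71 |
| 0.7 | 8.52 (1.84) | 0.80 | 7.86 (1.69) | 0.86 |

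The variance ratio is (1 − r²)/[2(1 − r)] = (1 + r)/2, that is 0.65, 0.75 and 0.85.

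If 11 is instead the SD of change, change-score power is 0.58 at every r, and ANCOVA gives 0.77, 0.71 and 0.65.

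**5. Interaction against change score when a 12-week effect exists (raw SD 11).** Interaction power is 0.46/0.61/0.83 for an effect of 5.2 at both T2 and T3, and 0.36/0.48/0.71 for 2.6 then 5.2. The change score has 0.45/0.58/0.80, so neither is uniformly better. ANCOVA is higher than both in each case.

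**6. Tukey.** At 12 weeks there are two groups and so one pair; nothing needs a pairwise correction. If Tukey ran over all six cells there would be 6 × 5 / 2 = 15 pairs, but the document does not say which pairs it covers.

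**The case against.** A reader might infer that the plan fails to test its 12-week endpoint at all. The text does not support that: a 12-week between-group comparison is planned, the primary time point is clear, and without T2 the interaction is that test. What remains is that this comparison is not singled out as primary.

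A reader might also take it as stated that baseline is a level of time. It is not; the model sentence lists only weeks 1, 6 and 12, and calculating differences from baseline is compatible with analysing change scores. The T1–T3 wording makes the baseline reading likely, but the text is inconsistent. Low power for a treatment main effect that averages in baseline would follow only if that main effect were the treatment test, which is nowhere said.

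Tukey need not contradict the statement on multiple testing, which may refer to multiplicity across outcomes while Tukey concerns pairs within one model.

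A change score is valid under randomisation, and a covariate list is often left to an analysis plan, which is not shown here. Silence about the covariate is therefore not an error. But the article does state a model and a testing sequence, and those can be improved.

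On χ², the article assigns no specific outcome to it, and no primary outcome is shown to be affected.

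**Conclusion.** The concern holds in a limited form and should be acted on. The stated route to the primary comparison is poorly matched to a single 12-week endpoint, and the deciding contrast is left open.

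If T2 is kept with baseline as a level, the omnibus interaction can be significant in about 46% to 83% of trials with no 12-week effect when T2 differs by 5.2 points. If T2 is dropped, the test is valid, and ANCOVA would add about 0.17, 0.13 and 0.06 to power at r = 0.3, 0.5 and 0.7, with 11 as the raw SD. Under the change-SD reading the gain is 0.19, 0.13 and 0.07.

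These sizes rest on an assumed r, equal correlations, an SD definition that the document does not give, and 43 analysed per group. The direction does not: ANCOVA variance is below change-score variance at any r under 1, apart from the one degree of freedom.

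The χ² point is sound in principle, because the test ignores order, but secondary. Any power loss there would be illustrative.

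**What to change.** Name one primary test for each primary measure: the treatment difference at 12 weeks from ANCOVA with the baseline score as covariate, reported with a 95% CI at the two-sided 5% level. A mixed model with baseline as covariate and a prespecified 12-week contrast would serve equally. Apply it to HAGOS daily living, VAS pain and the other continuous outcomes. Remove the omnibus-then-Tukey route for this comparison. State which measurements are levels of time in any longitudinal model, so that the week 1/6/12 and T1–T3 descriptions agree.

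For outcomes treated as ordinal, such as the EQ-5D levels, use a Wilcoxon test or proportional-odds regression, and keep χ² for nominal data. List which outcomes go to each.

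The cost is a change of wording in the protocol or analysis plan, made before the data are examined. It needs no new data and uses one degree of freedom per model.

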### Secondary hypotheses

There is evidence from RCT’s showing that a greater number of therapist contacts and higher intensity rehabilitation improves rehabilitation outcomes in patients with musculoskeletal pathology [21, 22]. This suggests a dose-response for treatment/training outcomes [23]. Class-based supervised exercise rehabilitation has also been shown to improve health outcomes compared to a non-supervised home-based group [24]. In our study a residential rehabilitation group will receive a period of intensive, supervised class-based treatment. An outpatient group will undergo a series of regular clinic appointments combined with unsupervised home-based exercise. We will test the following secondary hypothesis:ii.In patients with non-arthritic hip pain, residential MDT treatment, compared to outpatient physiotherapist led care, will result in a significant:Improvement in hip muscle strength (as measured by hand-held dynamometry)Increase in hip range-of-motion (as measured by inclinometer)Improvement in health related quality-of-life (as determined by the EuroQuol-5D)Greater adherence to home-based exercise (as determined by patient self-report diary)

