***The Visual Analogue Pain Scale***
*.* A visual analogue scale (VAS) will be used to measure pain intensity. The patient will be asked to rate their worst hip/groin pain experienced over the past 24-h using a 100 mm horizontal VAS anchored by the terms ‘no pain’ and ‘worst pain possible’. The supervising physiotherapist will also enquire if the sensation of pain is sharp or a dull ache, and if pain is made worse by movement. The 100-point VAS scoring requires no mathematical transformation, and with a normal distribution of data, it allows for parametric statistical analysis [60]. The VAS response format has shown good internal consistency, is easy to understand, is in wide clinical use, and has been sufficiently evaluated in clinical trials [60, 61].

The secondary outcome measures and instruments will be:
***EuroQuol-5D(EQ-5D-3L)***. The EQ-5D is a standardised, validated questionnaire for the self-rating of a patient’s health status [62]. It comprises a visual analogue scale (VAS) measuring self-rated health and a health status instrument consisting of a three-level response (no problems, some problems and extreme problems) for five domains [63]; (a) mobility, (b) self-care, (c) usual activities, (d) pain and discomfort and (anxiety and depression). A respondents EQ-VAS gives self-rated health on a scale where the endpoints are labelled ‘best imaginable health state’ (100) and ‘worst imaginable health’ (0). The EQ-5D has been shown to provide more exact ratings of everyday activities and their disease-related restrictions compared with other measures of health related quality of life (QOL) [64]. The inherent consistency of the EQ-5D test has been evaluated in the literature and shown good responsiveness to change in patients with hip conditions [65], and has been used in similar populations with similar musculoskeletal complaints to our study population [66].

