***Adherence to Home Exercise***
*.* Low adherence to home based exercise programmes is widely accepted as a key contributor to poor long-term clinical rehabilitation outcomes [85, 86]. To measure adherence during the 3-month follow-up period, participants in this study will be asked to maintain a diary/log-book recording the frequency, duration and intensity of the exercises in their home-based programme. Participants will also rate their adherence to the home programme at 3-months on an 11 point rating scale (with 0 being ‘not at all’ and 10 being ‘completely as instructed’). This method of measuring adherence to home-based exercise has previously been used in hip rehabilitation randomised controlled studies [5, 29].

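### Ordinal data are assigned to the same unordered chi-square test as nominal data, which loses power wherever the rule is applied to an ordered secondary measure

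*Protocol article*

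**What the plan says.** In the Statistical analysis section, continuous variables go to a mixed-model repeated-measures ANOVA. The next sentence gives a fallback: "The non-parametric equivalent or data transformation will be used if non-normal distributions apply". Categorical data have a separate rule: "Differences in nominal/ordinal data will be analysed using the" chi-square test. The same section adds: "All tests will be two-sided and carried out at the 5 % level of significance". No rank, trend or ordinal-model method is named for ordinal data.

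The protocol does not say which outcomes count as ordinal, but it describes two ordered measures:

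- The EQ-5D-3L, under Outcome measures, has a "three-level response (no problems, some problems and extreme problems) for five domains". The same instrument includes a self-rated health scale from 0 to 100.
- Under Adherence to Home Exercise, participants keep a diary and also rate their adherence at 3 months "on an 11 point rating scale".

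Two of the secondary hypotheses touch these instruments: "Improvement in health related quality-of-life (as determined by the EuroQuol-5D)" and "Greater adherence to home-based exercise (as determined by patient self-report diary)".

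**The concern.** Pearson's chi-square statistic is unchanged if the category labels are shuffled. On a scale with k levels it spreads its sensitivity over k − 1 degrees of freedom, whereas a rank, trend or proportional-odds test concentrates it on one, the movement up or down the scale. The secondary hypotheses are about such movement. The chi-square test also yields no effect estimate and makes no use of a baseline level, although the EQ-5D is measured at baseline.

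This is a method the protocol states, not a detail left open. If it is followed for an ordered measure, a real difference is more likely to be missed than it need be.

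**Working it through.** **Inputs from the protocol.** Chi-square test for ordinal data and two-sided 5% level (Statistical analysis); 43 per group after dropout and 100 recruited, so 50 per group (Sample size); 3 levels for an EQ-5D-3L domain; 11 levels for the adherence rating.

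**The plan's own figure.** No power is stated for any ordinal outcome, so there is none to reproduce. The 43 per group is for the HAGOS subscale, and it does not follow from its stated inputs: 2 × (1.960 + 0.842)² × (11/5.2)² = 2 × 7.849 × 4.475 ≈ 70.2, hence 71 per group. That is a separate matter. Here 43 and 50 serve only as the likely numbers analysed per arm.

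**Step 1: degrees of freedom alone.** Take an ordered effect that a 1-df test detects with 80% power, so the noncentrality is (1.960 + 0.842)² = 7.849. Give the same noncentrality to the general chi-square test with k − 1 df:

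| Levels | df | Power |
|---|---|---|
| order-respecting test | 1 | 0.80 |
| 3 | 2 | 0.71 |
| 7 | 6 | 0.52 |
| 11 | 10 | 0.43 |

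**Step 2: simulation.** 10,000 trials per scenario, Pearson chi-square against the tie-corrected Wilcoxon-Mann-Whitney test, two-sided 5%. The protocol gives no category distributions or effects, so these are assumptions: proportional-odds shifts with odds ratio (OR) 2, 2.5 or 3. Power at 43 per arm, chi-square vs rank test:

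| Assumed distribution | OR 2 | OR 2.5 | OR 3 |
|---|---|---|---|
| 3 levels, 30/60/10% | 0.261 vs 0.340 | 0.425 vs 0.538 | 0.599 vs 0.704 |
| 3 levels, 50/45/5% | 0.275 vs 0.368 | 0.471 vs 0.582 | 0.620 vs 0.729 |
| 3 levels, even | 0.319 vs 0.404 | 0.505 vs 0.608 | 0.666 vs 0.769 |
| 11 levels, even | 0.148 vs 0.437 | 0.269 vs 0.669 | 0.398 vs 0.823 |
| 11 levels, skewed high | 0.134 vs 0.438 | 0.248 vs 0.664 | 0.369 vs 0.804 |

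By subtraction, the loss is 7.9 to 11.3 points for three levels and 28.9 to 43.5 points for eleven. At 50 per arm the ranges are 8.7 to 10.9 and 32.0 to 42.9.

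**Step 3: other assumptions.** A three-level item at 30/55/15% with OR 2.5 gives 47% vs 58%. An 11-point rating with mean 6.5 and SD 2.5 gives 32% vs 75% for a 1.5-point shift and 59% vs 94% for 2 points. These tell the same story.

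**Step 4: sparse cells.** An even spread over 11 categories gives 43/11 = 3.9 or 50/11 = 4.5 expected per cell. In the 11-level simulations 58% to 75% of expected counts were below 5 with no true difference. At 43 per arm the chi-square test then rejected in 3.1% to 3.9% of trials, so it is somewhat conservative, not inflated.

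**The case against.** A reader might infer that the adherence and EQ-5D hypotheses are themselves headed for false null results. The documents do not support that.

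- **Adherence.** The hypothesis names the diary. The diary records frequency, duration and intensity, and the Home-based programme section sets a goal of at least 80% of prescribed sessions. That gives a percentage, which goes the continuous route, or a yes/no variable, for which chi-square is correct. The 11-point rating is an additional item.
- **EQ-5D.** The hypothesis names only the instrument, and its 0-100 scale fits the mixed model.
- **Classification.** Nothing states that the 0-10 rating is handled as ordinal. If it is treated as continuous, the non-parametric fallback is available.
- **Direction.** Frequencies and percentages are to be presented by group, so the direction will be visible even though the test does not address it.
- **Scope.** This is a condensed article, and the test for each variable is often left to an analysis plan.

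The first four points stand, and they limit the reach of the concern. The last does not answer it: the article fixes a test for ordinal data, and its non-parametric fallback is attached to continuous variables. The silence on which outcomes are ordinal limits what can be claimed and is also a reason to name them.

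**Conclusion.** The rule for ordinal data is poorly chosen. Wherever it is applied, order is discarded and power is lost: moderately for a three-level EQ-5D-3L domain (about 8 to 11 points at 43 per arm) and heavily for an 11-point scale (about 30 to 43 points). The sizes rest on assumed distributions and shifts that the protocol does not supply; chi-square had the lower power in every scenario tried.

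The heavy loss falls on the supplementary adherence rating, if that is treated as ordinal, and not clearly on a named hypothesis. HAGOS, NAHS and VAS pain are scored as continuous, so the primary comparison is untouched. Nor do the sparse cells show inflated false-positive error. This is a secondary-outcome matter, worth correcting because the correction is nearly free.

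**What to change.** Amend the sentence so that chi-square (or Fisher's exact test where cells are sparse) applies to nominal data only. For ordinal outcomes name an order-respecting method: a Wilcoxon rank-sum or trend test, or a proportional-odds model that includes the baseline level where one was measured, reported as an odds ratio with 95% CI. The adherence rating is made at 3 months and has no baseline, so a rank-sum test is enough there.

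State which secondary outcomes this covers, and which measure tests each hypothesis: diary or rating for adherence; domains or the 0-100 scale for the EQ-5D.

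The cost is a sentence or two, with no extra data and no change to the sample size. The section already commits to documenting and justifying changes to the analysis plan; this one should be recorded before the data are analysed.
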